### Sequence Generation, Allocation Concealment Mechanism, Implementation, and Blinding

This pragmatic field trial does not use a control group. Therefore, sequence generation, allocation concealment, implementation, and blinding are not discussed.

### Data Collection Methods

Data collection in the BAM is completely automated through its website. Therefore training of personnel is irrelevant. All data collection forms will be equal for each new participant who subscribes to the program. For collection of the descriptive lifestyle data, questionnaires have been used that accurately represent the relevant health norm or health behavior (full lifestyle questionnaires can be found in Multimedia Appendix 2). For measuring cognitive functioning, the BAM program uses a validated online self-monitor for cognitive functioning, specifically developed for use in the BAM, called the BAM-COG [47]. We have deliberately chosen to keep the baseline assessment as concise as possible. Creating a complete overview of a participant’s lifestyle can be a tedious task and with high risk of early dropout in eHealth interventions, the BAM’s lifestyle assessment is meant to give a fast and easy overview of a participant’s compliance to health norms, not a detailed description of all facets that make up healthy living.

The BAM intervention has multiple built-in mechanisms aimed at increasing retention to protocol. As described in the intervention section of this protocol, we will use blogs and recipes in the intervention to keep participants’ focus on the program, as well as the deployment of the adjustable reminder system and the flexible use of newsletters. When the program has been online for 365 and 730 days, special newsletters will be sent out to all active participants reminding them of their annual follow-up measurement that becomes available on their personal dashboard.

Participants who want to exit the study can do so at any time. They can unsubscribe from their personal profile page using the unsubscribe instructions. Once this process is initiated by the participant, a short questionnaire will be used to identify the reason for dropout. Also, the BAM will ask the participant if they are still willing to be reminded of the annual measurements. In this case, they would not actively participate in goal setting and behavior monitoring but would be willing to come back and provide the program with follow-up data.

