After all baseline data are collected, the tailored knowledge databases, the buddy system, healthy recipes, and blogs on health behavior and cognitive aging become available. The buddy system is a built-in control mechanism the BAM uses to ensure goal safety. A subset of goals that are suitable for this purpose are anonymously sent to another BAM user to be judged by a BAM buddy on its feasibility and safety. A buddy can judge a goal to be “ambitious”, “not ambitious enough”, “just right”, or in the case of losing weight, “this seems unhealthy”. This gives the goal-setter an opportunity to get instant feedback on the feasibility of their goal. Also, it gives the buddy a “look behind the scenes” that may provide feedback on their own goal-setting behavior, as the exact same situation for somebody else may be perceived as harmful whereas this same goal would be deemed applicable to the participant themselves. At the same time that the buddy system becomes available, participants also get access to the knowledge databases that contain up-to-date information on healthy living and the relationship between the different behaviors and brain health. Last, participants get access to weekly blogs on lifestyle, research and brain aging, and healthy recipes. After 365 and 730 days upon completion of the baseline measurement, they will be recruited for 1-year and 2-year follow-up measurements.

No reasons for discontinuation of the study of a participant by the research team have been specified. There is no disease load that can be exacerbated by participating in the BAM nor is there any medication prescribed that could have negative health consequences. Participants are provided with the option of unsubscribing to the study at any given time in their personal profile space. When a participant decides to leave the program, a short questionnaire is automatically presented to collect data on the reason for unsubscribing and to inquire if the participant may be approached to partake in the 1-year and 2-year measurement, regardless of subscription status. All of this is voluntary and participants can always choose to skip this questionnaire.

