Keeping participants engaged with eHealth intervention programs has been a major problem since the field originated [7,57,58]. Several adherence-enhancing strategies are in place with the BAM. First, we upload weekly news updates on the homepage regarding health behavior and brain aging from the largest Dutch news websites. Second, on the dashboard of the participant we will upload weekly blogs and healthy recipes so that the content, apart from user input, changes on a weekly basis. Blogs discuss current topics in research on anything BAM-related in an easy accessible form. Recipes use fresh and healthy products and provide participants with ideas to prepare a healthy meal. Third, a personalized email reminder system is built into the BAM that can be adjusted to the participants’ individual needs. In their personal profile space, a participant can choose to receive daily, weekly, biweekly, or monthly email reminders. These reminders give an overview of current active goals and will link the participant directly to this goal after logging in. Fourth, during the registration process new participants can opt in to receive BAM newsletters, which will be sent using the MailChimp engine. At any time, participants can opt in or opt out of the newsletter. Last, participants get a personal profile space with a quick and easy overview of their current lifestyle. They can make adaptations to their lifestyle, see the results of their goals, and can adjust their settings.

Considering the field setting for this intervention, it is difficult to control for concomitant care, or better yet if the BAM inspires participants to make use of other platforms to alter their health behavior in a positive way, this accomplishes the BAM’s goals. The BAM can and may function as a gateway to healthy behavior. Using the GSM and the yearly follow-up, the BAM can track changes over time even if participants actively use outside help that the BAM refers them to.

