### Participant Timeline

The timeline for the BAM is straightforward (see Figure 1). Participants need to register only once. Immediately after registering, email validation, and the informed consent form, the lifestyle questionnaires are available. Once the lifestyle questionnaires have been completed, the BAM-COG becomes available. Seven days after subscription, the personality questionnaires appear in the personal dashboard. These features are all presented again to the participant 365 and 730 days after their baseline completion. The GSM, STMS, and LTMS are continuous processes from the moment they first become available to the participant. After 1 year (365 days), the data will be collected for preliminary secondary outcome analysis. After the 2-year follow-up (730 days), the data will be used for analysis of both primary and secondary outcomes. The nature of the grant requires that the intervention remain online even after data collection is finished for the initial study period and that the BAM remain open to the public after the study is completed. Adaptations to the program can be made at this time, according to study outcomes.

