### Recruitment

Different recruitment strategies will be implemented to reach the necessary sample size. First, we will recruit medium to large commercial or governmental organizations through their human resources department or company employed medical staff. The BAM can provide organizations with a concrete intervention program that can substantiate their health policy. Organizations will be recruited by direct inquiry through telephone calls, emails, and will be targeted during several symposia, workshops, and congresses where the BAM will be presented. Once an organization is recruited, the research team in collaboration with the human resources department will develop a tailored recruitment strategy that maximizes the use of existing communication channels within the organization. These organizations are expected to deliver approximately 50% of all study participants.

Next to organizational recruitment, the BAM will also recruit participants in the general Dutch population. A press release will be issued by the Radboudumc to reach mainstream media to generate national attention for the study. The BAM will be advertised at the website of a cooperative research consortium that draws national attention because researchers from four nationally spread out universities will promote this website. Also, we will present the BAM at national and international health care conferences. We estimate that approximately 50% of all study participants will result from this free recruitment strategy.

The enrollment period will take approximately 4-5 months. However, due to the nature of the grant no actual stop in participant influx will be enforced. Participants will be allowed to enter the study at any given time. We will monitor participant influx over time so we can keep estimating the relevance and need for an intervention such as the BAM. Unless individual organizations determine otherwise, no financial incentives will be offered to potential participants. If this occurs, this will be disclosed in future publications.

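### The annual follow-up reminder runs on the programme's clock, while the measurement falls due on each participant's own clock, so the reminder comes too early for everyone who completes baseline after launch day

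*Protocol article*

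**What the plan says.** All references are to the protocol article.

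- **Reminder.** Data Collection Methods, in its paragraph on retention: "When the program has been online for 365 and 730 days, special newsletters will be sent out to all active participants", with the purpose of "reminding them of their annual follow-up measurement that becomes available on their personal dashboard".
- **When the measurement opens.** Participant Timeline, on the questionnaires and the cognitive battery: "These features are all presented again to the participant 365 and 730 days after their baseline completion".
- **When participants are approached.** Intervention: "After 365 and 730 days upon completion of the baseline measurement, they will be recruited for 1-year and 2-year follow-up measurements". No channel is named.
- **Entry.** Recruitment: "The enrollment period will take approximately 4-5 months". The same paragraph says that influx will not be closed and adds: "Participants will be allowed to enter the study at any given time".
- **Leavers.** Data Collection Methods, on people who unsubscribe: "the BAM will ask the participant if they are still willing to be reminded of the annual measurements". The Intervention section likewise asks leavers whether they may be approached for the yearly measurements whatever their subscription status.
- **Other e-mails.** The personal reminders in the Intervention section are described as covering active goals. Annual follow-up is not mentioned there.

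**The concern.** The reminder is timed from the day the website went live. The event it announces is timed from each participant's own baseline. With staggered entry these are different dates, and the gap grows with every day a participant joins after launch.

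The timing matters because of how the study is built. The primary outcomes are changes from baseline to years 1 and 2, and there is no control group. The Secondary Analyses section states that analysis is per protocol and that dropout is likely to be high. A participant who does not return at follow-up contributes no change score. The Sample Size section aims for 200 with 166 needed, a margin of 200 - 166 = 34 people. A retention measure that fires at the wrong time wastes a cheap chance to keep people within that margin.

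**Working it through.** The plan states no figure for reminder timing, so there is nothing to reproduce. The check is date arithmetic.

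**Inputs from the article**
- Newsletter sent on programme days 365 and 730 (Data Collection Methods).
- Measurement opens 365 and 730 days after own baseline completion (Participant Timeline; the Intervention section agrees).
- Enrolment of about 4-5 months, with no stop in entry (Recruitment).
- Personality questionnaires appear 7 days after subscription (Participant Timeline).

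**Assumptions, not in the article**
- Entry is spread evenly over the enrolment period, starting on launch day.
- A month is 30.4375 days, so 4 months = 121.75 days and 5 months = 152.19 days.

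**Lead time for one participant.** Let B be the programme day on which baseline is completed.
- Year 1: the measurement opens on programme day B + 365 and the newsletter goes out on day 365. Lead = (B + 365) - 365 = B.
- Year 2: lead = (B + 730) - 730 = B.

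The newsletter is early by B days both times. It is on time only if B = 0. This needs no assumption about the pattern of entry.

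**Size under even entry over T days.** The mean lead is T/2, the maximum is T, and the share reminded more than k days early is 1 - k/T.

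| Enrolment | Mean lead | Maximum | More than 30 days early | More than 60 days early |
|---|---|---|---|---|
| 4 months | 121.75/2 = 61 days | 122 days | 1 - 30/121.75 = 75% | 1 - 60/121.75 = 51% |
| 5 months | 152.19/2 = 76 days | 152 days | 1 - 30/152.19 = 80% | 1 - 60/152.19 = 61% |

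If the personality questionnaires count towards baseline completion, at least 7 days are added. The means become 61 + 7 = 68 and 76 + 7 = 83 days, and the maxima 122 + 7 = 129 and 152 + 7 = 159 days.

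**Example.** Someone completing baseline at the end of month 5 (B = 152) gets the year-1 newsletter on own day 365 - 152 = 213 and the year-2 newsletter on own day 730 - 152 = 578.

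**Late entrants.** Someone who joins after programme day 365 was not a participant when the year-1 newsletter went out. Their own year-1 measurement opens after programme day 365 + 365 = 730, so the second newsletter also reaches them before it opens. Someone who joins after day 730 gets neither.

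**After correction.** Timed from own baseline completion, the lead is 0 days for everyone.

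**The case against.** The best defence is that the newsletter is only an extra announcement. The Intervention section says that participants will be recruited for follow-up at their own 365 and 730 days, and the dashboard presents the instruments again on those dates. Regular goal e-mails also bring users back to the site. This stands in part: the newsletter cannot be called the only prompt. But the Intervention section names no channel, and the goal e-mails are not described as mentioning follow-up. The newsletter remains the only reminder specified in detail.

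A second defence is loose wording: the phrase about the programme being online may have been meant as each participant's time in the programme. That is possible, and the article is a condensed account. The sentence still says something else, and an automated system has to be built to one clock or the other.

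A third is that people entering a year or more after launch may not belong to the analysis cohort. The article does not say either way. The early reminder for those entering in the first 4-5 months does not depend on them.

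Four stronger readings are tempting, and the article does not support them:
- *Participants would complete the 12-month measurement early, on receiving the newsletter.* The instruments are presented only on the participant's own date, so someone reminded on own day 213 has nothing to complete.
- *People who opted out of newsletters would be missed.* The Intervention section does say "At any time, participants can opt in or opt out of the newsletter", but the special newsletters are addressed to all active participants. Nothing shows that the opt-out applies to them.
- *Consenting leavers would certainly be lost.* Asking them whether they may be reminded or approached implies a contact route. The article just does not describe it.
- *A stated amount of follow-up will be lost.* The article gives no basis for turning lead time into missing data.

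**Conclusion.** The conflict is real and internal to the article: Data Collection Methods uses a programme clock, while Intervention and Participant Timeline use a participant clock. As written, the newsletter is early for everyone who completes baseline after launch day, by exactly the number of days since launch.

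The direction and the B-day rule rest on the text alone. The averages of about 61-76 days and the maxima of about 122-152 days rest on even entry over 4-5 months from launch; a different accrual pattern would change the averages. The loss of the year-1 newsletter for entrants after programme day 365 follows from open entry.

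The expected consequence is a mistimed or missing prompt, and so some avoidable missing follow-up in an uncontrolled per-protocol study that already expects high dropout. How much cannot be derived. The timing of the assessments themselves is not compromised. The sentence should be corrected; it does not by itself invalidate the follow-up.

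**What to change.** Reconcile the reminder sentence in Data Collection Methods with Intervention and Participant Timeline:

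1. Trigger the reminder on day 365 and day 730 after each participant's own baseline completion, using the same date that opens the instruments on the dashboard.
2. State that it goes to active participants and also to unsubscribers who agreed to be reminded.
3. In the Intervention section, say whether this reminder is the means by which participants are recruited for follow-up or whether there is another channel.

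The cost is one change to an automated e-mail trigger and a sentence or two of text. Data collection is already fully automated, and the measurement schedule and sample size are unaffected.

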After a participant has decided which instructions and tips to use, the goal gets transferred to the short-term monitoring system (STMS). Here, participants can monitor their own behavior on a day-to-day basis. Inputting their behavior in the STMS, the system automatically graphs a quick overview of how well a participant is doing for that goal on a week-to-week basis. After a month, the STMS asks the participant to what extent the goal is accomplished on their own original GAS scale. For any score specific to that goal, the BAM gives tailored feedback. If a score of -2 or -1 is obtained, the goal is deleted from the participant’s profile and encouragement to try again is given. However, if a score of 0, 1, or 2 is obtained, the goal gets transferred to the long-term monitoring system (LTMS). In the LTMS, a participant gets monthly follow-up questions to monitor if they still are maintaining their initial level of behavior change. With every monthly question that gets answered, the participant is given tailored feedback to acknowledge their success or motivate the participant to maintain their initial behavior change. Multiple goals can be graphed over time giving a personal overview of all acquired and maintained behavior change goals. If multiple goals are set on the same subject, new goals will overwrite old goals so that only the most up-to-date information is shown. Because the BAM does not dictate how many a goals a participant sets and in what order they do this, it implicitly provides the participant with a conceptual choice between simultaneous or sequential goal setting, giving every participant the option to work at their own pace and preference [50-52].

In order not to overload the participant with questionnaires immediately after registering, the personality questionnaires become available to the participant 7 days after registration. These are the Dutch General Self-Efficacy Scale [53], lifestyle factor specific self-efficacy questions [54], the Positive Affect Negative Affect Scale [55], and the Self-Control Scale [56]. These questionnaires are administered to perform secondary analyses to check if the BAM is more effective in certain personality types. No feedback on the personality questionnaires is provided for the participants.

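### The annual follow-up newsletter is timed from programme launch but the measurements from each participant's own baseline, so each newsletter precedes the measurement it announces for essentially every recipient

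*Protocol article*

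**What the plan says.** Two timing rules are stated for follow-up.

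- **Reminder, programme clock.** Data Collection Methods, in its paragraph on retention: "When the program has been online for 365 and 730 days, special newsletters will be sent out to all active participants". The stated purpose is "reminding them of their annual follow-up measurement that becomes available on their personal dashboard".
- **Measurement, participant clock.** Participant Timeline: "These features are all presented again to the participant 365 and 730 days after their baseline completion". Intervention says the same: "After 365 and 730 days upon completion of the baseline measurement, they will be recruited for 1-year and 2-year follow-up measurements".

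Three further statements determine how far apart the clocks run.

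- **Entry.** Recruitment: "The enrollment period will take approximately 4-5 months". The same paragraph adds that intake is not closed after that and that people may join later.
- **Start of the participant clock.** Intervention: "the personality questionnaires become available to the participant 7 days after registration". Participant Timeline repeats this: "Seven days after subscription, the personality questionnaires appear in the personal dashboard". Intervention then moves directly to what opens once baseline data are complete, but the article does not define baseline completion.
- **Individual e-mails.** Intervention describes adjustable personal reminders: "These reminders give an overview of current active goals and will link the participant directly to this goal after logging in". The annual measurement is not mentioned among their contents.

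**The concern.** A reminder sent on one calendar date cannot match a measurement that opens on a different date for each person. A recipient who logs in because of the newsletter would usually find that the measurement it announces is not yet open.

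The 12- and 24-month measurements supply the change scores for all three primary outcomes, and Participant Timeline reserves the primary analysis for the 2-year data. The programme is self-guided, contact with the research team is limited to technical support, and Secondary Analyses expects high dropout. The newsletter is one of the retention tools the article names, and its timing works against its purpose. The second newsletter, on programme day 730, is the last follow-up reminder the article describes, and it goes out before year 2 opens for almost everyone.

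**Working it through.** The plan gives no lead time to reproduce; the check is date arithmetic.

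**Inputs**

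- e = programme day on which a participant enters. Planned window 4-5 months (Recruitment), that is 4 × 30.44 ≈ 122 to 5 × 30.44 ≈ 152 days. Later entry is allowed.
- b = days from entry to baseline completion. At least 7 if the personality questionnaires count as baseline (Intervention, Participant Timeline); possibly 0 if they do not.
- Newsletters on programme days 365 and 730 (Data Collection Methods).
- Assumption: enrolment starts on the day the programme goes online. If it starts later, every lead is longer.

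**Formulas**

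- Year 1 opens on programme day e + b + 365, and year 2 on e + b + 730.
- Lead of the first newsletter over year 1 = (e + b + 365) − 365 = e + b.
- Lead of the second newsletter over year 2 = (e + b + 730) − 730 = e + b, the same number.
- Time year 1 has already been open at programme day 730 = 730 − (e + b + 365) = 365 − (e + b).

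**Results (days)**

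| Entry day e | Lead, b = 7 | Lead, b = 0 | Year 1 open by day 730, b = 7 |
|---|---|---|---|
| 0 | 7 | 0 | 358 |
| 122 (4 months) | 129 | 122 | 236 |
| 152 (5 months) | 159 | 152 | 206 |
| 300 | 307 | 300 | 58 |
| 364 | 371 | 364 | opens 6 days later |

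- **Planned window.** The lead is 7 to 159 days with b = 7 (159 / 30.44 ≈ 5.2 months) and 0 to 152 days with b = 0. If baseline takes 30 days, it is 30 to 182 days.
- **Late in year 1.** Entry on day 364 with b = 7 gives 371 days, or 371 / 30.44 ≈ 12.2 months. Five months is therefore not an upper limit.
- **After day 365.** These participants miss the first newsletter. With entry on day 500 and b = 7, year 1 opens on day 500 + 7 + 365 = 872, which is 142 days after the day-730 newsletter. Year 2 opens 507 days after it.
- **On the participant's own clock.** A reminder on own day 365 or 730 has a lead of 0 for everyone, whatever e and b are.

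**The case against.** The strongest reply is that this is one loosely worded sentence about a newsletter. Two sections state the measurement schedule clearly, and the newsletter sentence can be read as advance notice. Several parts of that reply stand.

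- **The newsletter may not be the only prompt.** Intervention says participants will be recruited to follow-up on their own clock. Data Collection Methods asks people who unsubscribe whether they may still be reminded, which suggests a route beyond a mailing to active participants. A condensed article may leave such mechanics out, so its silence does not show that no other prompt exists.
- **There is not always nothing to complete.** At programme day 730, planned-window entrants have had year 1 open for 206-358 days (b = 7), and no closing date is given. Only year 2 is still shut.
- **Not every participant is affected in the same way.** The mailing goes to active participants, and newsletters are described as opt-in. If baseline excludes the day-7 questionnaires, someone who completes it on launch day has a lead of zero.

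A reader might also infer that the 1-year and 2-year intervals become short and unequal, so that change scores mix with season. That would require the dashboard to open for everyone on the programme date. Intervention and Participant Timeline both say otherwise.

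A reader might try to express the problem as lost power, using the 166 and 200 in Sample Size. The article does not link newsletter timing to any follow-up rate, so such figures would measure an assumed dropout and not this defect.

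The advance-notice reading does not remove the mismatch. Notice that comes about a week ahead for one person and five to twelve months ahead for another does not work as a reminder, and people who enter after day 365 receive no first notice.

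**Conclusion.** The point holds as a contradiction in timing. The newsletter runs on the programme clock and the measurements on the participant clock. With staggered entry, each newsletter comes e + b days before the measurement it announces.

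For the planned window that is about 1 week to 5 months, or 0 to 5 months if the day-7 questionnaires are not part of baseline. Open intake extends it to about 12 months for people who enter late in year 1, and later entrants miss the first newsletter. These figures assume that enrolment starts at launch.

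The consequence is a mistimed retention tool for the data behind the primary outcomes. The stated measurement schedule, the outcomes and the analysis are not altered, and the size of any loss to follow-up cannot be derived from the article. This is an inexpensive consistency correction that is worth making, not a flaw that invalidates the design.

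**What to change.** Reconcile Data Collection Methods with Intervention and Participant Timeline. Replace the two programme-date newsletters, as follow-up reminders, with an automatic e-mail triggered on each participant's own day 365 and day 730 after baseline completion. It should link directly to the measurement and also go to leavers who agreed to be reminded. State which instruments must be finished for baseline to count as complete, since that starts the clock.

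Data collection is already automated and a personal e-mail system is described, so the cost is one changed e-mail rule and one corrected sentence, plus a short definition. No extra data, staff or participants are needed. Repeating the e-mail until the measurement is completed, and using actual days since baseline in the models, are optional.
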